---

### PROTOCOL SYNOPSIS

**Title:** A Comparison of Success Rates and Complications between Different needle insertion approaches for Landmark-Guided Femoral Vein Cannulation

**Study Type:** A prospective, single-center, Randomized Controlled, Clinical Trial

**Corresponding Author:** [name], Department of Anesthesiology, Shanghai East Hospital, Tongji University School of Medicine, Shanghai, China. [name], Department of Anesthesiology, Shanghai East Hospital, Tongji University School of Medicine, Shanghai, China.

**Study Center:** Shanghai East Hospital, Tongji University School of Medicine

**Ethics:** Approved by the Ethics Committee of Shanghai East Hospital (Approval No. 2024YS-280).

**Trial Registration:** [www.chictr.org.cn](http://www.chictr.org.cn) (ChiCTR2500096775)

---

## I. STUDY OBJECTIVES

Central venous catheterization is a critical clinical procedure for diagnostics and treatments such as fluid resuscitation, blood transfusion, chemotherapy, and central venous pressure monitoring, and is widely used in critically ill patients [1, 2]. Currently, there is a lack of systematic research and statistical analysis regarding the efficacy and safety of different needle insertion approaches for landmark-guided femoral vein puncture. This study aims to compare the success rates and safety of different needle insertion directions during landmark-guided femoral vein puncture, aiming to provide references and inspire new insights for healthcare practitioners in clinical practice.

## II. BACKGROUND

### A. Challenges of Femoral Vein Catheterization

Among the commonly used central venous access routes, the femoral vein is a vital option, particularly recommended when superior routes are obstructed. It offers advantages like a large lumen and stability in hypovolemic patients [3]. However, its main challenge lies in the high anatomical overlap between the femoral artery and vein within the femoral triangle, which can exceed 70% just 2 cm below the inguinal ligament [4]. This overlap significantly increases the risk of complications—such as arterial puncture, hematoma, infection, and thrombosis—during the commonly used "blind palpation" or landmark-guided technique [5]. Despite the clear superiority of ultrasound guidance endorsed by major medical societies, its availability is often limited in real-world clinical settings, especially in emergencies, primary care hospitals, and under-resourced regions. Therefore, mastering and optimizing the traditional landmark technique remains a necessary skill for clinicians, underscoring the pressing need to improve its safety and efficacy.

### B. Anatomical Overview of the Femoral Vein

The conventional landmark technique relies on palpating the femoral artery as a reference, with the standard puncture point being 2-3 cm inferior to the inguinal ligament and 0.5-1.0 cm medial to the arterial pulse, advancing the needle parallel to the artery (a "medial and parallel" approach) [6, 7]. Given the high prevalence of the femoral vein lying directly beneath the artery (classified as Types II and III by Guan et al.), this traditional anterior approach may frequently miss the vein or risk traversing the artery [8]. To address this anatomical challenge, an alternative "lateral-medial" needle direction has been proposed [9]. In this approach, the needle is inserted from the same medial starting point but is angled towards the femoral artery. The rationale is that this lateralward trajectory may better target the vein when it is situated posteriorly (in a deep position) relative to the artery, potentially improving the first-pass success rate and reducing the number of attempts and associated complications.

### C. Preliminary Studies

Currently, there is a lack of robust, comparative studies systematically evaluating the efficacy and safety of different needle insertion directions for landmark-guided femoral vein puncture. To fill this evidence gap, our study is designed as a prospective randomized controlled trial. We will compare the traditional "medial and

parallel" approach with the innovative "lateral-medial" approach in patients requiring landmark-guided femoral vein cannulation. Key outcomes measured will include the first-attempt success rate, overall success rate, number of puncture attempts, procedural time, and the incidence of immediate complications. By providing high-level evidence on the optimal needle direction, this research aims to establish a simple, no-cost modification to a fundamental clinical skill. The findings are expected to offer valuable guidance for anesthesiologists, intensivists, and emergency physicians, ultimately enhancing patient safety in diverse clinical environments where ultrasound is not immediately available.

### III. METHODS

This is a prospective randomized, controlled trial that has been registered in the Chinese Clinical Trial Registry (ChiCTR2500096775) and has been approved by the Ethics Committee of Shanghai East Hospital (Approval No. 2024YS-280). This report adheres to the CONSORT guidelines. The study was conducted according to the guidelines of the Declaration of Helsinki with Good Clinical Practice. All participants provided written informed consent before enrolment.

#### A. Recruiting Methods

Potential participants to the study were identified from the elective surgery list. Patients aged  $\geq 18$  years, ASA I to IV, and undergoing femoral vein puncture and catheterization in our hospital were eligible to participate. The study will involve the use of protected health information. The study site will gain permission from each subject to use their protected health information by written authorization. All subjects will be identified by the anesthesiologist.

#### B. Inclusion Criteria

Patients aged  $\geq 18$  years, ASA I to IV, and undergoing femoral vein puncture and catheterization in our hospital were eligible to participate.

#### C. Exclusion Criteria

Exclusion criteria encompassed: thrombotic or inflammatory involvement of target vasculature; localized infections at puncture sites (e.g., tinea cruris); prior femoral/pelvic vascular surgery; pre-existing inguinal hernia; and peripheral artery disease.

#### D. Consent Procedure

All potential subjects that are identified by the chief anesthetist and/or designee that meet the inclusion/exclusion criteria will be given the opportunity to participate. Guardians/patients will be given the consent/assent during the screening visit. They will be given the opportunity to review the consent/assent and ask questions about the study. Guardians/patients will be asked to summarize in their own words what participation in this research study involves and that they are comfortable with the risks and benefits of participating in the research study. Any additional questions they have will also be answered by the investigator prior to signing the consent/assent. Once the consent/assent form is signed, a signed and dated copy of the authorization form will be provided to the subject and another copy placed in the participant's medical record.

## **E. Randomization and Blinding**

Randomization was performed using a computer-generated random numbers table with a 1:1 allocation ratio. The allocation sequence was sequentially numbered and sealed in opaque envelopes by the corresponding author. The anesthesiologists opened the envelopes 10 minutes before the procedure commenced. Due to the nature of the intervention, full blinding of all study personnel was not feasible. However, to minimize bias, we attempted to blind the patients, research assistants, and data analysts. To achieve patient blinding, during the informed consent process, we described all interventions as femoral vein catheterization, and we explained that depending on group allocation, patients might receive different puncture trajectories.

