## **H. Intervention and Study Procedures**

During the access procedure, we adjust the patient to a supine position with a slight external rotation of the hips (the "frog-legged" position). Landmarks such as the anterior superior iliac spine, pubic symphysis, and inguinal ligament were identified. The femoral artery pulse was palpated 2-3 cm below the midpoint of the inguinal ligament and puncture was performed at 1-2 cm medial to the femoral artery. After sterile prep and a small subcutaneous dose of lidocaine, the needle was inserted steeply downward at a 30°-45° angle into the skin in different directions according to the patient's grouping and the timer was initiated. Crossover to the ultrasound-guided puncture occurred after three unsuccessful attempts. The timer was stopped when the puncture needle entered the target vessel or after three unsuccessful attempts. All patients underwent a puncture of the right femoral vein in this study.

Based on the relationship between the femoral vein and artery, Guan et al. classified the anatomy into four types (Fig. 3): Type I (vein parallel to artery without overlap),

Type II (vein medial to artery with lumen overlap  $\leq 50\%$ ), Type III (vein posterior to artery with lumen overlap  $> 50\%$ ), and Type IV (vein lateral to artery) [9]. After the puncture catheterization, vascular ultrasonography was used to evaluate the femoral vasculature anatomy in the puncture area of each patient.

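### The operator learns the arm before choosing the entry point within a range, and the entry point is neither marked nor recorded, so it could come to differ by arm

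*Protocol*

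**What the plan says.** Protocol III.E (Randomization and Blinding) describes sequentially numbered, sealed, opaque envelopes and states: "The anesthesiologists opened the envelopes 10 minutes before the procedure commenced". It concedes that not everyone can be blinded. Of those it does try to blind, it says "we attempted to blind the patients, research assistants, and data analysts"; operators are not on that list.

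Protocol III.H (Intervention and Study Procedures) opens with "During the access procedure, we adjust the patient to a supine position" and goes on to landmarks, palpation and puncture. The pulse is felt at a level given as a range of 2-3 cm below the ligament. For the entry site it says "puncture was performed at 1-2 cm medial to the femoral artery". The needle then goes in "in different directions according to the patient's grouping".

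Protocol II.B (Anatomical Overview) describes the alternative approach: "the needle is inserted from the same medial starting point but is angled towards the femoral artery". For the conventional approach it places the puncture point "0.5-1.0 cm medial to the arterial pulse".

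Protocol III.I (Measurements and Endpoints) lists six recorded items. The entry point, or its distance from the pulse, is not among them.

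**The concern.** Randomization balances the patients. It does not balance choices that the operator makes after learning the allocation. Here one such choice, where to enter the skin, bears directly on the comparison. The trial's stated aim is to compare needle directions, which presupposes that direction is the only thing that differs between arms.

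Someone about to angle the needle towards the artery may have a geometric reason to prefer a different medial offset from someone about to go parallel to it. If so, the offset would vary with the arm while staying inside the permitted range, and no protocol deviation would be logged. The contrast between arms would then be direction plus entry point. Because the offset is not recorded, no later analysis could detect the difference, adjust for it, or show that it was absent.

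**Working it through.** **1. Order of steps.**

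| Step | Where stated | Timing |
|---|---|---|
| Envelope opened by the operator | III.E | 10 minutes before the procedure starts |
| Patient positioned | III.H | during the access procedure |
| Landmarks found, pulse palpated | III.H | next in the same description |
| Puncture 1-2 cm medial to the artery | III.H | next in the same description |
| Direction set by group | III.H | at insertion |

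The order of opening and palpation is inferred from the two sections read together. Neither section states it outright, but the inferred order is the natural reading.

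**2. Room for choice.** The medial offset has a range of 2 − 1 = 1 cm. The palpation level also spans 3 − 2 = 1 cm, but III.H gives that as the place where the pulse is felt; only the medial offset is stated for the puncture itself. No section fixes a single distance or calls for a mark.

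**3. Design figures (III.F).** Inputs: 90% against 60%, two-sided 0.05, power 0.90.

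n = [1.96·√(2·0.75·0.25) + 1.2816·√(0.9·0.1 + 0.6·0.4)]² / 0.30² = 41.7, so 42 per group, as stated. Allowing for 20% attrition, 42/0.8 = 52.5, so 53; the protocol uses 54. The design inputs are confirmed.

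**4. Illustration of size.** The protocol does not say how success depends on entry point, so no bias can be derived from it. The assumptions are: direction has no effect; success is 60% in one arm; entry choice alone raises the other arm by b. The chance of a two-sided 5% result favouring the raised arm is approximately

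Φ[(b − 1.96·s₀)/s₁], with s₀ = √(2·p̄(1 − p̄)/n) and s₁ = √(p₁(1 − p₁)/n + p₂(1 − p₂)/n).

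For b = 0.10 and n = 54: p̄ = 0.65, s₀ = 0.0918, s₁ = 0.0913; (0.10 − 0.1799)/0.0913 = −0.875; Φ = 0.191. Summing the exact binomial probabilities over all chi-square results significant in that direction gives 0.196.

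Exact values:

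| Assumed shift b | 42 per group | 54 per group |
|---|---|---|
| 0 points | 2.9% | 2.5% |
| 5 points | 7.4% | 7.9% |
| 10 points | 16.5% | 19.6% |
| 15 points | 31.6% | 38.8% |

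**5. Sign.** If the shift instead put the lateral arm 10 points lower (60% against 70%), the chance of a result favouring it would be about 0.1% at 54 per group and 0.2% at 42, below the nominal 2.5%. The bias could run either way.

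**The case against.** The strongest reply is that III.H gives both arms one entry rule and makes only direction depend on the group. Variation within the range that is unrelated to arm is noise, not confounding. The operator must in any case know the arm before inserting the needle, so the 10-minute interval is not itself the defect: opening one minute before palpation would carry the same risk. All of this stands. What remains is that the operator need not know the arm when choosing the entry point, and that nothing recorded would reveal a difference.

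A reader might infer more than the protocol supports:

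- **That entry points do differ by arm, so the trial cannot attribute a difference to direction.** The text shows only that an arm-dependent choice is possible.
- **That the bias favours the lateral approach.** Nothing in the protocol says that a more medial start helps. II.B reasons that the vein often lies beneath the artery, so a start further away could just as well hurt that arm.
- **That early opening lets difficult patients be withdrawn once the arm is known.** III.D places eligibility and consent at screening, III.C has no criterion on difficult palpation, and no section provides for such withdrawals.
- **That allocation concealment fails.** The concern is performance after allocation. The numbered, sealed, opaque envelopes are not in question here.

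**Conclusion.** The point holds as a risk of performance bias that is cheap to reduce. On the plain reading of III.E and III.H, the entry point is chosen within a 1 cm medial range by an operator who already knows the arm, and III.I does not capture it. Whether the choice would in fact differ by arm, in which direction and by how much cannot be learned from the protocol.

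The percentages above rest wholly on the assumed shift, the 60% base rate and the absence of a direction effect. They show that even a 5-point shift would roughly triple the chance of a false result towards the favoured arm, from about 2.5-3% to 7-8%. They do not estimate what this trial will show.

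Separately, the medial distances in II.B (0.5-1.0 cm) and III.H (1-2 cm) meet only at 1.0 cm. The investigators need to reconcile them; this review takes no position on which applies.

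**What to change.** Amend III.E and III.H so that the steps run in this order:

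1. Position the patient and palpate the pulse.
2. Mark the first entry point on the skin, within the range that the investigators set, and record its offset from the pulse.
3. Open the envelope.
4. Make the first puncture at the mark.

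Add the entry offset of every attempt to the items recorded under III.I, and report offsets by arm.

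The cost is one skin mark and one or more recorded values per patient. The operator also has less time between learning the arm and puncturing.

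The protection is partial. It covers mainly first-attempt success. Up to three punctures are allowed, and the second and third are still placed by an operator who knows the arm, so overall success, number of attempts and puncture time stay exposed; the recorded offsets would at least make any difference visible.

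Parts of the protocol are written in the past tense. If enrolment is already complete, the remaining step is to state this limitation and report by arm whatever entry-point data exist.

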## **F. Sample Size Calculation**

PASS 2021 (NCSS, East Kaysville, UT, USA) was employed for sample size computation. A small, non-blinded, unpublished pilot study with 20 participants indicated that the puncture success rates for the lateral and orthogonal approaches were 90% and 60%, respectively. With a two-sided error of 0.05 and a power of 0.9, the sample size for each group was calculated as 42. To account for 20% attrition, we increased the sample size to 54 per group. In sensitivity analyses, even with conservative assumptions (risk ratio=1.3 or 30% attrition), the original sample size maintained over 80% power.

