## **G. Statistical Analysis**

Continuous variables were presented as mean (SD) or median (interquartile range, [IQR]), depending on whether the data was distributed normally or not. Categorical variables were presented as a number (percentage). The normal distribution of data was evaluated using the Shapiro–Wilk test, and the Levene method was used to test the homogeneity of variance. Differences in repeated measures variables were analyzed by repeated-measures analysis of variance. Continuous outcomes were analyzed with one-way analysis of variance (ANOVA) or Kruskal-Wallis test. Categorical variables were tested using  $\chi^2$  test or Fisher's exact test. Time-to-event outcomes were illustrated using Kaplan-Meier curves. For a post hoc sensitivity analysis, we employed a logistic regression model. Statistical significance was defined as  $P < 0.05$ . Statistical analysis was conducted using SPSS v27.0 (SPSS Inc., Chicago, IL, USA).

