## **I. Measurements and Endpoints**

The following parameters were systematically recorded for all enrolled patients:

(1) First-attempt Success Rate: Defined as the successful aspiration of venous blood through the needle on the initial skin puncture, without any needle withdrawal or redirection. This metric primarily reflects the precision of the initial puncture technique.

(2) Overall Success Rate: Defined as the ultimate successful aspiration of venous blood, achieved within a maximum of three puncture attempts or before the occurrence of any significant complication necessitating termination of the procedure.

(3) Number of Puncture Attempts: This refers to the total count of separate skin punctures required to achieve successful venous blood aspiration. Each withdrawal of the needle tip completely from the skin followed by a new puncture constitutes a new attempt. Minor redirections of the needle beneath the skin without complete withdrawal are not counted as separate attempts.

(4) Puncture Time: Measured in seconds, from the moment the needle first touches the skin until the successful aspiration of venous blood. The timer is stopped immediately upon confirmation of free venous blood flow into the syringe.

(5) Procedure-related Complications: All adverse events occurring during or immediately after the puncture procedure were meticulously documented. These include, but are not limited to accidental arterial puncture, hematoma formation, pneumothorax, etc.

(6) Anatomic Relationship between the Femoral Vein and Artery.

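### The sample size rests on a puncture success rate that matches neither defined success endpoint, and the protocol names no primary endpoint

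*Protocol*

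**What the plan says.** - **Sample size (Protocol III.F).** The assumption comes from a 20-participant pilot: "the puncture success rates for the lateral and orthogonal approaches were 90% and 60%, respectively". Then: "With a two-sided error of 0.05 and a power of 0.9, the sample size for each group was calculated as 42", and "To account for 20% attrition, we increased the sample size to 54 per group".
- **Endpoints (Protocol III.I).** Six recorded parameters stand in a numbered list, none marked primary or secondary. Two are success rates. First-attempt success is "Defined as the successful aspiration of venous blood through the needle on the initial skin puncture", with no withdrawal or redirection allowed. The other is "Overall Success Rate: Defined as the ultimate successful aspiration of venous blood", reached within at most three attempts.
- **Key outcomes (Protocol II.C).** "Key outcomes measured will include the first-attempt success rate, overall success rate, number of puncture attempts, procedural time, and the incidence of immediate complications". They are not ranked.
- **Significance (Protocol III.G).** "Statistical significance was defined as" P < 0.05, once, without reference to any particular endpoint.
- **Synopsis and Study Objectives (Protocol I).** Neither names a primary endpoint; the objectives speak of success rates and safety in general.

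**The concern.** A power statement means something only for a named endpoint. The pilot's success rate could be either of the two success endpoints in III.I. Overall success includes every first-attempt success and adds successes from later attempts or after redirection, so the two rates, and the contrast between the arms, can be quite different.

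Without a named primary, the protocol also leaves open which result decides the trial. Either success rate, the number of attempts, the time or the complications could become the headline after the data are seen, each judged at 0.05. The 5% error and 90% power in III.F would then describe neither the conclusion that is drawn nor the endpoint it is drawn from. The operator cannot be blinded here, so fixing the deciding endpoint in advance is one of the few safeguards available.

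**Working it through.** **1. Reproduce the stated sample size.** Inputs from III.F and III.E: 90% vs 60%, two-sided 0.05, power 0.90, and 1:1 allocation ("Randomization was performed using a computer-generated random numbers table with a 1:1 allocation ratio"). Pooled-variance formula without continuity correction, mean rate 0.75:

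n = [1.960·√(2·0.75·0.25) + 1.2816·√(0.9·0.1 + 0.6·0.4)]² / 0.30² = (1.200 + 0.736)² / 0.09 = 41.7, so 42 per group.

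Power at 42 is 90.2%. For attrition, 42/0.8 = 52.5, so 53; the protocol's 54 is close enough. At 54 per group with no loss, power is 96.0%. The arithmetic is sound.

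**2. What if 90%/60% are first-attempt rates?** The protocol gives no overall rates, so an assumption is needed.
- *Three independent attempts, each with the first-attempt success chance.* Overall success is 1 − 0.1³ = 99.9% vs 1 − 0.4³ = 93.6%. Power is 37% at 42 per group and 45% at 54 (normal approximation, rough this close to 100%).
- *Mixed difficulty in the control arm.* Suppose 80% of patients have per-attempt success 0.725 and 20% have 0.10. First-attempt success is 0.8·0.725 + 0.2·0.10 = 60%. Overall success is 0.8·(1 − 0.275³) + 0.2·(1 − 0.9³) = 83.8%. Against this control rate at 54 per group:

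| Overall success, lateral arm | Power |
|---|---|
| 92.7% | about 30% |
| 96.3% | about 59% |
| 97.5% | about 69% |
| 99.9% | about 88% |

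The first three lateral rates are compatible with 90% first-attempt success under similar mixes; the last is the independence value. Across these assumptions, power for overall success runs from about 30% to 88%.

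**3. What if 90%/60% are overall rates?** With independent attempts, first-attempt success is 1 − 0.1^(1/3) = 53.6% vs 1 − 0.4^(1/3) = 26.3%. Power is 73% at 42 per group and 83% at 54; 90% power would need 66 per group before attrition.

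**4. Error for the conclusion with two success endpoints.** If the two tests were independent, 1 − 0.95² = 9.75%. They are correlated. Simulating no difference at 54 per group, with 60% first-attempt and about 84% overall success in both arms, at least one was significant in about 9% of trials, while each test alone stayed near 5%.

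**The case against.** Several objections are fair, and they limit the point.

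- *The sample size is correct.* It is. A reader might infer from the unclear label that 42 or 54 is miscalculated; step 1 shows otherwise.
- *Each test has a 5% error.* True. A reader might infer that the 5% holds nowhere. It holds test by test; what is missing is control over a conclusion that may rest on any of several tests. Nor does III.G say that any one significant result makes the trial positive. It simply does not say which result does.
- *The two success rates may have been equal or close in a pilot of 20.* Possible. It would be too strong to say that 90%/60% can describe only one of them; the protocol does not tell us.
- *The power figures rest on invented models.* They do. Under III.I, redirection beneath the skin does not count as a new attempt, yet it disqualifies first-attempt success, so the per-attempt chance is not strictly the first-attempt rate. The independence and mixed-difficulty models also give different control rates (93.6% and 83.8%). The figures show how far power can move and do not estimate it.
- *Multiplicity rules belong in the SAP.* A detailed adjustment procedure may well be there, and its absence here is not held against the protocol. The primary endpoint and its link to the sample size are different: the protocol should fix both.
- *First-attempt success is listed first, so it is the implied primary.* List order is a hint only. The remark in III.I that this metric primarily reflects precision describes what it measures and gives it no rank. Nothing in III.F says that the pilot rates are first-attempt rates.

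**Conclusion.** The point stands in this form: 90% vs 60% is tied to neither defined success endpoint, and no endpoint is named primary. The stated 90% power therefore attaches to no identified endpoint, and the overall conclusion has no 5% error control.

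Its size depends on facts the protocol does not give. In most of the cases worked through, the success endpoint that the pilot did not measure falls well short of 90% power; in the most favourable it comes close, at about 88%. The error inflation for the two success rates alone is modest, about 9% instead of 5%. It would be larger if attempts, time and complications could also become the headline, but no figure for that can be given without assuming distributions that the protocol does not contain. This should be settled in the protocol, because it decides what the trial can claim.

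**What to change.** 1. In III.F, state which III.I endpoint the pilot's 90% and 60% measured. Only the investigators can supply this.
2. In III.I, name one primary endpoint, tested once at two-sided 0.05. First-attempt success is the natural candidate: the rationale in II.B is about first-pass success, and it is listed first in II.C and III.I. The choice remains with the investigators.
3. If the pilot measured the other success endpoint, restate the power for the named primary, with the assumed rates and their source.
4. Label the remaining outcomes secondary, with no confirmatory claim.

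The cost is protocol wording and the loss of confirmatory status for the other outcomes. No extra data are needed, and 42 per group (54 with attrition) stands if the named primary is the endpoint the pilot measured. If it is not, the restated power may fall below 90%.

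### The claimed power above 80% at a risk ratio of 1.3 is wrong: with the protocol's own 60% control rate it is about 43% (42 per group) to 53% (54 per group)

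*Protocol*

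**What the plan says.** All the figures are in Protocol section III.F (Sample Size Calculation).

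- **Effect.** A pilot study in 20 participants suggested that "the puncture success rates for the lateral and orthogonal approaches were 90% and 60%, respectively". That is a difference of 30 points and a risk ratio of 1.5.
- **Base size.** "With a two-sided error of 0.05 and a power of 0.9, the sample size for each group was calculated as 42".
- **Inflation.** "To account for 20% attrition, we increased the sample size to 54 per group".
- **Robustness.** "In sensitivity analyses, even with conservative assumptions (risk ratio=1.3 or 30% attrition), the original sample size maintained over 80% power".

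Section III.E gives equal allocation, and section III.G names the chi-square test or Fisher's exact test for categorical outcomes. The protocol gives no success rates for the risk-ratio scenario, and does not say whether the original sample size is 42 or 54 per group.

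**The concern.** A risk ratio of 1.3 is a much smaller effect than the one the trial was sized on. From a 60% control rate, the gain shrinks from 30 points to 18. Required sample size varies roughly with the inverse square of the difference, so a trial with 90% power at 30 points cannot be expected to keep 80% at 18 points.

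The planning effect comes from a pilot that the protocol itself describes as small, non-blinded and unpublished, so a smaller true effect is a real possibility. This sentence is the only place where the protocol says what happens then. An ethics committee or reader relying on it would believe that a gain from 60% to 78% would very probably be detected. If the chance is in fact about even or worse, a non-significant result would carry far less information than the protocol implies.

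**Working it through.** **Inputs (section III.F unless noted).** Success 0.90 lateral and 0.60 orthogonal; two-sided alpha 0.05 (z = 1.960); target power 0.90 (z = 1.2816); 42 per group, raised to 54; equal allocation (III.E).

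**Step 1: reproduce the stated 42.** For the pooled two-proportion z test without continuity correction, with p̄ the mean of the two rates:

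n = [1.960·√(2p̄(1−p̄)) + z_power·√(p₁(1−p₁) + p₂(1−p₂))]² / (p₁−p₂)²

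With p̄ = 0.75: [1.960·√0.375 + 1.2816·√0.33]² / 0.30² = (1.2002 + 0.7362)² / 0.09 = 41.7, so 42. The stated figure reproduces (power 90.2%). The continuity-corrected formula gives 49, the unpooled 39 and the one-sided 34, so the pooled two-sided test is evidently the one used. Inflation for 20% attrition is 42/0.8 = 52.5, so 53; the stated 54 covers it.

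**Step 2: same test, risk ratio 1.3 on the stated control rate.** The lateral rate is 1.3 × 0.60 = 0.78, the difference 0.18 and p̄ = 0.69.

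Power = Φ{[√n·(p₁−p₂) − 1.960·√(2p̄(1−p̄))] / √(p₁(1−p₁) + p₂(1−p₂))}

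Here 1.960·√0.4278 = 1.2819 and √(0.1716 + 0.24) = 0.6416.

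- n = 42: (6.4807 × 0.18 − 1.2819)/0.6416 = −0.180, power 42.9%
- n = 43 (54 less 20%): −0.158, power 43.7%
- n = 54: (7.3485 × 0.18 − 1.2819)/0.6416 = 0.064, power 52.5%

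For 80% power: (1.2819 + 0.8416 × 0.6416)² / 0.18² = 102.4, so 103 per group.

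**Step 3: does the choice of test matter?** For 78% versus 60%, two-sided 0.05:

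| Method | 42 per group | 54 per group |
|---|---|---|
| Pooled z | 42.9% | 52.5% |
| Unpooled z | 44% | 54% |
| Wald test on log risk ratio | 42% | 51% |
| Chi-square, exact enumeration | 44% | 53% |
| Fisher's exact | 35% | 45% |

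**Step 4: the kinder anchor.** Hold the lateral arm at 0.90, so the control is 0.90/1.3 = 0.692. Pooled power is 66.2% at 42, 67.2% at 43 and 77.2% at 54. Exact enumeration of the chi-square test gives 68.6% at 42 and 78.9% at 54. By the pooled formula, 80% needs 58 per group.

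**Step 5: when would the claim be true?** At a risk ratio of 1.3, 80% power needs a control rate of about 70% with 54 per group, or about 73% with 42. The lateral rate would then be about 91% to 95%, above the pilot's 90%. The protocol gives no such control rate.

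**Step 6: the attrition half, at 90% versus 60%.**

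- From 54: 54 × 0.7 = 37.8, so 37 left, power 86.2%. The claim holds.
- From 42: 42 × 0.7 = 29.4, so 29 left, power 76.5%. It falls short with the pooled test.

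**The case against.** The strongest objection is that the protocol never says which rates lie behind the risk ratio of 1.3, so the 60% anchor is an inference. If the lateral arm stays at 90% and all 54 per group are analysed, power is 77.2% by the pooled test, 78.9% by exact chi-square, 79.2% by the unpooled test and 79.6% by a likelihood-ratio test. On that reading the claim misses by about 0.4 to 3 points. This is a fair limit on how large the error must be. It does not make the claim true: every figure is below 80%, all assume no attrition, and with 42 per group the same reading gives only 66% to 69%. A one-sided 0.05 test on that reading at 54 per group would reach 86%, but the protocol specifies a two-sided error.

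Second, the attrition half should not be counted as another error. On the sensible reading, attrition applies to the 54 recruited, and the claim holds. Even from 42 the answer depends on the test (76.5% pooled, 80.3% unpooled). That point stands; what remains is only the ambiguity over which number is meant.

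Third, the sentence sets no design parameter: the 42 is correct and the 54 is adequate for the planning effect. That is also right. It limits the remedy to the text, but does not excuse a false numerical statement in the sample-size justification. Nor does the protocol say that a non-significant result will be read as no difference; that risk lies with readers.

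**Conclusion.** The concern holds. At the only control rate the protocol gives, power at a risk ratio of 1.3 is 43% with 42 per group and 53% with 54, against a claim of more than 80%. The overstatement is at least 27 points at 54 per group and 37 at 42. Anchoring on the 90% lateral rate narrows the gap to about 3 points at 54 per group and 14 at 42, but does not close it.

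This rests on the pooled two-sided 0.05 test, which reproduces the protocol's own 42, and on one of the two stated success rates applying in the scenario. The planning calculation itself and the attrition claim counted from 54 per group are not in question.

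**What to change.** Delete the risk-ratio claim in section III.F, or replace the sentence with figures that name the two rates, the number analysed and the test. Suggested text, using the pooled two-sided test at 0.05:

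> With 54 evaluable patients per group, power is 96% for 90% versus 60%, 80% for 84% versus 60% (risk ratio 1.40) and 53% for 78% versus 60% (risk ratio 1.30). With 43 per group after the planned 20% attrition, the corresponding figures are 91%, 70% and 44%. With 30% attrition (37 per group), power is 86% for 90% versus 60%.

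The 43-per-group figures belong there because the protocol expects that loss; quoting 54 alone would again show the more favourable number. The 70% comes from the Step 2 formula with p̄ = 0.72: (√43 × 0.24 − 1.960·√0.4032)/√0.3744 = 0.538, and Φ(0.538) = 0.70.

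The text should also say which number the original sample size refers to. If the authors used another control rate for the risk-ratio scenario, they should state it and justify it. Optionally, add that a non-significant result will be interpreted through the 95% confidence interval of the risk difference.

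The cost is a short passage of protocol text. No extra patients are needed and the design does not change; the trial simply gives up a claim of robustness that it does not have.
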